**Figure 4. F4:**
[figure not shown]
CONSORT (Consolidated Standards of Reporting Trials) study flowchart of HELI (Hersenfuncties na LeefstijlInterventie) study participant enrollment, screening (inclusion and exclusion), randomization, and allocation.

The baseline measurements at the DCCN and WUR centers were successfully completed by October 2023. The baseline mean age of our sample population was 66.6 (4.3) years, of which 65.7% (n=67) was female (see Table 2). The mean total years of education was 16.2 (SD 4.6) years. At baseline, 9.8% (n=10) of participants had a low level of education (International Standard Classification of Education [ISCED] 0‐2), 34.3% (n=35) had a medium level of education (ISCED 3‐4), and 55.9% (n=57) had a high level of education (ISCED 5‐8). The median risk, measured by points on the self-reported lifestyle-modifiable risk factor scale, was 3 (IQR 2‐3) points. The most common self-reported lifestyle-modifiable risk factors of cognitive aging at baseline were overweight or obesity (76/102, 74.5%), hypertension (58/102, 56.9%), hypercholesterolemia (57/102, 55.9%), and physical inactivity (57/102, 55.9%). See Table 2 for an overview of the HELI study baseline characteristics.

**Table 2. T2:** Baseline characteristics of the HELI (Hersenfuncties na LeefstijlInterventie) study (n=102).

Characteristic	Value	
Participant demographics		
Age (years), mean (SD)	66.6 (4.3)	
Sex (female), n (%)	67 (65.7)	
Educational level, n (%)^a^		
Low	10 (9.8)	
Medium	35 (34.3)	
High	57 (55.9)	
TICS-M1 score, mean (SD)	29.0 (3.6)	
Self-reported inclusion factors		
Overweight and obese (BMI ≥25), n (%)	76 (74.5)	
Obese (BMI ≥30), n (%)	35 (34.3)	
Physically inactive, n (%)^b^	57 (55.9)	
Hypertension, n (%)^c^	58 (56.9)	
Hypertension medication usage, n (%)	84 (82.4)	
Hypercholesterolemia, n (%)^d^	57 (55.9)	
Diabetes type II, n (%)	20 (19.6)	
Mild cardiovascular disease, n (%)^e^	11 (10.8)	
Risk severity		
Risk factor score, median (IQR)	3 (2-3)	

a Based on the International Standard Classification of Education (ISCED 2011) guidelines (low, medium, and high education categorization).

b Based on nonadherence to the WHO Guidelines on physical activity (300 or more min of moderate aerobic activity or 150 min of vigorous aerobic activity per wk).

c Based on systolic blood pressure of ≥140 mm Hg and diastolic blood pressure ≥90 mm Hg.

d Based on total cholesterol >5mmol/L or LDL-cholesterol of >3 mmol/L.

e Based on mild cardiovascular disease not mentioned in exclusion criteria (eg, varicose veins and atherosclerosis).

## Discussion

### Principal Findings

We described the design of the HELI study, an RCT focusing on the mechanisms of a 6-month multidomain lifestyle intervention in Dutch older adults at risk of cognitive decline, by assessing functional and structural MRI-related brain measures as well as peripheral measures related to the gut-immune-brain axis. The study design is based on the design of the FINGER-NL trial [108] and optimized for assessment of mechanisms instead of effectiveness.

The HELI study is characterized by its unique multimodal approach, which enables us to obtain mechanistic insights of a multidomain lifestyle intervention. We are using a broad range of neuroimaging techniques (see Table S3 in Multimedia Appendix 1 for the MRI sequence protocol) and neurocognitive tests to acquire a comprehensive profile of brain health. In addition, we also measure an extensive set of peripheral intestinal and immunometabolic markers, allowing us to investigate gut-immune-brain interactions and discover mediators of lifestyle effects on brain health. Combined with questionnaire data on lifestyle compliance, these brain, blood, and fecal markers have the potential to provide an elaborate overview of the pathways involved in lifestyle effects on cognitive aging and to explain individual differences in effectivity.

Compared to previous 24-month multidomain lifestyle interventions in cognitive aging [3,18,19,164] and the FINGER-NL trial [108], the HELI study intervention of 6 months is significantly shorter. However, our multidomain lifestyle intervention was carefully modified from the 2-year FINGER-NL intervention into a more condensed and intensified 6-month program. Especially, the high-intensity intervention group was characterized by more frequent meetings and group contact, requiring higher weekly effort. Within the field of functional neuroimaging, the duration of HELI (26 weeks) is relatively long compared to other (single-domain) lifestyle intervention studies (6‐9 weeks), which reported significant central mechanistic intervention effects [52,54]. The main focus of our study is on the underlying mechanisms of lifestyle adaptations on cognitive aging, rather than on trial effectiveness. Therefore, we consciously chose to use multiple specific brain and peripheral parameters as primary outcomes, instead of cognitive functioning. We expect these parameters to be more sensitive to lifestyle changes, and therefore to be affected in an earlier stage than cognitive functioning.

We ultimately managed to include a total of 102 participants within our study. Our study population shares a similar baseline lifestyle modifiable risk factor profile (CAIDE) compared with the FINGER study, based on the total number of participants with hypertension, hypercholesterolemia, and diabetes (see Table S5 in Multimedia Appendix 1 [165-167]). Other previous multidomain lifestyle intervention studies in older adults, such as the pre-DIVA, MAPT, and J-MINT studies, used inclusion criteria different from the CAIDE-related lifestyle modifiable risk factors, or included participants solely based on age. Compared with previous studies, our study population is relatively highly educated, and we were unable to include a comparable number of participants with a lower education level. However, many of these earlier studies completed participant inclusion over a decade ago, and education levels have generally increased over time, which may reflect cohort effects. Because education level is often used as a covariate in task-related neuroimaging outcomes and neuropsychological test data, this is an important limitation to consider during data interpretation and comparison of results with other studies. For a more detailed description of the baseline characteristic comparison between the HELI study and previous multidomain lifestyle intervention studies, see Table S5 in Multimedia Appendix 1.

To summarize, the most important strength of the HELI study is its unique combination of multimodal neuroimaging and peripheral phenotyping with a multidomain lifestyle intervention. Moreover, the study has several additional strengths. First, the design has two active arms, which promote blinding and intervention adherence, while preserving between-group comparisons of lifestyle interventions. Second, the group approach within the high-intensity group is a strength, as it encourages peer support and intervention adherence. Finally, the online-onsite combination establishes a future-oriented intervention framework that ensures both quality and broad applicability. Limitations of the study comprise the limited number of objective domain-specific adherence measures and the selection bias toward more highly educated individuals, potentially due to the digital intervention format.

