There are numerous studies showing that gut microbiome composition and immune-metabolic health effects on the host are modified by diet and nutritional components [90-92], including the Mediterranean-type diets [93,94]. In addition, other lifestyle components such as physical activity [95,96], stress [97], and sleep [98,99] are known to affect the microbiota composition and intestinal health, as well as immune, vascular, and metabolic health [100-107]. Importantly, we hypothesize that multiple lifestyle domains can synergistically affect peripheral markers and should therefore be targeted simultaneously. However, it is still largely unclear how gut microbiome, immune, and metabolic factors link to brain health in aging, and which mechanisms are involved. By investigating how lifestyle-induced changes in these peripheral factors relate to changes in brain health, we can make stronger conclusions about the role of these peripheral-brain links in cognitive aging. Moreover, elucidating peripheral-brain mechanisms might also explain individual differences seen in lifestyle interventions for healthy cognitive aging.

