**Figure 2. F2:**
[figure not shown]
Overview of the study design. Schematic overview of study visits, assessments, and intervention groups. Before **T0 **and after **T1,** the intervention period of 6 months, participants visited the Donders Center for Cognitive Neuroimaging (DCCN) and Wageningen University and Research (WUR) study centers with one week in between.

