### Outcomes

All outcome measures were measured at baseline (T0) and after participation in the 6-month multidomain lifestyle intervention (T1), during visits at both research centers. Blood drawing and breath tests were performed in a fasted state. Some outcome measures, such as lifestyle domain or adherence-related questionnaires, were also collected throughout the intervention period. For a detailed overview of all outcomes and the collection schedule, see S4 in Multimedia Appendix 1.

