### Methods: Statistics and Analysis

We will test for change between T0 and T1 in the primary and secondary outcome variables, both within-group and between-group, using linear mixed-effect models with random effects for intercept (individuals). The intervention group and time will be included as fixed effects, as well as the interaction term between intervention group and time, to model the difference in change between T0 and T1 as a function of group allocation.

In addition, we will test for correlations in change (T0 minus T1) between (primary) brain outcomes and (primary) peripheral outcomes. We will select an appropriate correlation test for our data, based on whether assumptions are met. We will include both the high- and low-intensity groups if there is enough variance in change across both groups; else, we will only include the high-intensity group.

The level of significance will be set at 0.05 (2-sided). FDR correction will be used to account for multiple comparisons of secondary and exploratory outcomes. FWE correction will be used for secondary whole-brain analyses.

As part of exploratory analyses to assess the domain-specific effects on our primary outcome measures, we will take the pre- and posteffects of the primary outcome measures and use domain-related questionnaire scores and smartwatch-derived physiological data as a measure of improvement for each respective domain as predictors in linear mixed-effect models.

We will perform an intention-to-treat analysis. Participants who withdrew from the study during the 6-month intervention period, but had not withdrawn consent, were invited to the T1 (after week 26) follow-up outcome assessments. This means that we will use all available collected data, including collected (follow-up) data of participants who dropped out of the intervention. Missing data or data with insufficient quality, however, will not be used in the analysis.

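### The article says the trial can discover mediators, but its only stated marker-brain analysis is a correlation of concurrent changes; this cannot show direction, and pooling the arms without an arm term inflates false positives

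*Protocol article*

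**What the plan says.** Under Principal Findings in the Discussion, the extensive peripheral measurements are presented as "allowing us to investigate gut-immune-brain interactions and discover mediators of lifestyle effects on brain health".

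On timing, the Outcomes section states: "All outcome measures were measured at baseline (T0) and after participation in the 6-month multidomain lifestyle intervention (T1), during visits at both research centers". At each occasion the two centres were visited a week apart (Figure 2 caption: "study centers with one week in between"). Some measures were taken in between, but the examples are questionnaires: "Some outcome measures, such as lifestyle domain or adherence-related questionnaires, were also collected throughout the intervention period". The article names no blood, fecal or MRI measure between T0 and T1.

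On analysis, Methods: Statistics and Analysis plans correlations between change in the primary brain outcomes and change in the primary peripheral outcomes. Of the test it says: "We will select an appropriate correlation test for our data, based on whether assumptions are met". Both arms are to be included if change varies enough across them; otherwise only the high-intensity arm is used. No arm term is stated for these correlations. The exploratory mixed models in the same section take questionnaire and smartwatch scores as predictors, so they do not link blood or fecal markers to the brain outcomes.

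The limitations at the end of the Discussion concern adherence measures and selection by education. They do not mention this restriction.

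**The concern.** A mediator claim needs more than two measures that change together. Randomisation supports the effect of arm on the marker and the effect of arm on the brain outcome. It does not support the step from marker to brain, because neither change is randomised and neither is observed before the other. The coaching acts on diet, activity, stress and sleep at once, and the article's own Gut-Brain Axis section says these affect the microbiota as well as immune, vascular and metabolic health. A common cause is therefore a natural rival explanation.

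The analysis also has a more concrete fault. If the intervention works on both a marker and a brain outcome, the two arms differ in mean on both. A correlation pooled over arms picks up that difference even if, within each arm, the two changes are unrelated. The better the intervention works, the larger this artefact. The trial's main interest is mechanism, so a spurious gut-immune-brain link would bear on its central message.

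**Working it through.** **Inputs from the article.** Randomised: 102 (53 high-intensity, 49 low-intensity). Expected data loss: 15%. Effect size f(V) = 0.30, two-sided alpha 0.05, power 80%, stated requirement 90.

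**The plan's own figure.** For two groups and two occasions, lambda = f² × N = 0.09 × 90 = 8.1 with 1 and 88 degrees of freedom. Power is 0.804 (0.795 at N = 88), so 90 reproduces. It covers the group-by-time interaction only; the article gives no power for the correlations.

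**Evaluable numbers.** 53 × 0.85 = 45.05 and 49 × 0.85 = 41.65, taken as 45 and 41, total 86.

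**Assumptions, not in the article.** The arm effect is the same size d on both change scores. The reference value d = 0.6 reads f = 0.30 as d = 2f. Where a link exists, its size is 0.3.

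**Step 1. Correlation created by pooling when there is no link.** With p = 45/86 = 0.523, p(1 − p) = 0.2495, and unit variance within arms,

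r = p(1 − p)d² / [1 + p(1 − p)d²].

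The rejection rate is approximately Φ(−1.96 + δ) + Φ(−1.96 − δ), with δ = atanh(r) × √(86 − 3) = atanh(r) × 9.11.

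| d on both changes | induced r | δ | false-positive rate |
|---|---|---|---|
| 0.3 | 0.022 | 0.20 | 5.5% |
| 0.6 | 0.082 | 0.75 | 11.7% |
| 0.8 | 0.138 | 1.26 | 24.3% |
| 1.0 | 0.200 | 1.84 | 45.4% |

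Simulation of the same set-up (45 + 41 participants) gave about 12%, 24 to 25% and 46 to 47% at d = 0.6, 0.8 and 1.0. With adjustment for arm the rate was about 5% throughout. If the arm effects have opposite signs, the induced r is negative and the two-sided rate is the same.

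**Step 2. Can the correlation tell the causal structures apart?** Simulated with d = 0.6 and a link of 0.3 (20,000 runs):

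| True structure | pooled mean r | significant | high-intensity arm r | significant |
|---|---|---|---|---|
| marker drives brain | 0.31 | 84% | 0.30 | 52% |
| brain drives marker | 0.31 | 84% | 0.30 | 53% |
| unmeasured common cause only | 0.36 | 93% | 0.30 | 52% |

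The three are practically alike. The slightly higher pooled figure in the last row arises because there the arm acts at full strength on both changes. Within arms the correlation is 0.30 by construction in all three (for the common cause, √0.3 × √0.3 = 0.3). An arm term therefore removes the artefact in Step 1 but does not supply direction.

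**Step 3. The high-intensity arm alone.** This avoids the pooling artefact (about 5% false positives) but drops the randomised contrast and costs precision. The smallest r detectable with 80% power is tanh(2.80/√83) = 0.30 with 86 participants and tanh(2.80/√42) = 0.41 with 45. An arm-adjusted pooled analysis holds the error rate and keeps the larger sample.

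**The case against.** Several points on the other side stand.

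- **The aim and hypothesis are worded modestly.** The Objective speaks of mechanisms, the hypothesis of changes that correlate, and Primary Outcomes of a relation. Figure 1 is captioned as hypothesised. A reader might infer that the trial as a whole sets out to prove mediation, or that any significant correlation will be reported as a mediator. The article gives no such rule, and the overstatement is confined to the Discussion.
- **The comparative claim is defensible.** A reader might also fault the statement in the Gut-Brain Axis section that "we can make stronger conclusions about the role of these peripheral-brain links in cognitive aging". Relating changes within an intervention trial is stronger evidence than the mainly cross-sectional work the article describes. That sentence claims neither proof nor direction.
- **Mediation is not beyond reach under assumptions.** With a randomised arm and T0 and T1 data, an indirect effect can be estimated if one accepts no marker-brain confounding and a causal order. An analysis plan that is not shown may add such a model or an arm term, and the full collection schedule in the appendix is not shown either. Those assumptions would remain untestable here. A mid-trial sample would give order but would not remove confounding.
- **The artefact depends on the effect size.** It needs an arm effect on both measures and is negligible at d = 0.3.

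What remains is that the analysis stated in the article is a plain correlation, and the Discussion claims more for it than it can give.

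**Conclusion.** The point holds in a limited form. The stated marker-brain analysis supports associations of change and does not establish mediators. Pooled without an arm term, it has a false-positive rate per pair of about 12% at d = 0.6 and about 24% at d = 0.8, against 5%. These figures rest on 86 evaluable participants, equal arm effects on both changes, no true link, and no multiplicity correction. The value d = 0.6 corresponds to the article's own planning effect; larger values are illustrative. The inability to separate direction from common cause does not depend on these values. It follows from two changes measured over the same six months. The documents do not support the broader charge that the design or its objectives are misconceived.

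**What to change.** 1. In Methods: Statistics and Analysis, make the main version of each pooled marker-brain association of change one that adjusts for arm, by partial correlation or by regression with an arm term.
2. Under Principal Findings, replace the claim about discovering mediators with *identify candidate mediators (associations of change)*.
3. In the limitations, add that two concurrent measurement occasions cannot establish direction or mediation.
4. Optionally, add a sensitivity analysis adjusted for change in diet and activity scores, which are already collected. Read any adjustment for change in BMI with caution: the Gut-Brain Axis section places adipose tissue between dysbiosis and systemic inflammation, so BMI change may lie on the pathway. An association should not be required to survive these adjustments, since that could reject a true mediator.
5. Leave the comparative sentence in the Gut-Brain Axis section as it is.

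The cost is one extra term per model, two edits to the text and a more modest mechanistic claim. No new measurement is needed.

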### Conclusions

The HELI study offers a novel mechanistic approach by integrating multimodal neuroimaging and peripheral phenotyping with a multidomain lifestyle intervention in older adults at risk of cognitive decline. Results of the HELI study can help explain the previously observed small effect sizes of multidomain lifestyle interventions to prevent cognitive decline in aging, paving the way for personalized prevention strategies in the future.
